| Technical Summary (Max. 300 words) *Background*  The population is ageing and consequently, the number of people living with age-related chronic conditions is increasing. Polypharmacy (five or more prescribed medications) is common in older people and is associated with an increased risk of adverse drug reactions. Preventative medications, such as those used to manage blood pressure and cholesterol, are common in polypharmacy and often require large numbers of people to be treated to prevent a small number of cardiovascular disease (CVD) events. This leaves many individuals on drugs of little benefit, some of whom may be susceptible to side effects such as falls, kidney problems and muscle pain.  *Aims*  This proposal aims to quantify the harms of cardiovascular prevention medication, and the characteristics of those people most likely to suffer them. This research is one part of a larger research programme to develop a clinical decision tool which estimates an individual’s likelihood of benefiting or suffering harm from treatment.    *Methods*  Aim 1: Derive prognostic models for an individual’s risk of adverse events associated with cardiovascular prevention treatment (antihypertensives, statins and antiplatelets) using data from the CPRD GOLD. Adverse event outcomes will include falls (antihypertensives), myopathy (statins) and bleeding (antiplatelets).  Aim 2: Externally validate each model using data from the CPRD Aurum.  Aim 3: Use causal inference methods (propensity score matching, instrumental variable analysis) to examine whether modification of treatment could have an important impact on the risk of adverse events. |

| Outcomes to be measured **Primary outcomes** - Falls; Myopathy/muscle pain; Intracerebral haemorrhage  **Secondary outcomes** – Fracture; Syncope; Hypotension (symptomatic); Acute kidney injury; Electrolyte abnormalities; Gout; Diabetes mellitus; Intracerebral haemorrhage; Cataract; Liver dysfunction; Dementia; Memory problems (including dementia); Gastrointestinal haemorrhage; Dyspnoea; Any adverse event  Specific outcomes will be examined in relation to exposure to either antihypertensives, statins or antiplatelets (details given in section N). |
| --- |

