| Study Type Hypothesis testing |
| Study Design Longitudinal cohort study |
| Feasibility counts There are approximately 5.5 million patients in England, aged 40+ and with up to standard registration for a period between 1/1/1998 to 31/12/2017 in the CPRD GOLD. Restricting to English practices (linked to HES and ONS) and only including patients fulfilling the eligibility criteria listed below, the expected population is approximately 3.3 million and out of these we expect 216,000 fall events, 230,000 myopathy/muscle pain events and 1,200 intracranial haemorrhage events. |
| Sample size considerations We have based our sample size calculation on the least common of the primary outcomes listed above (intracranial haemorrhage), and used the method developed by Riley *et al.,*^40^ to minimise the potential for overfitting and ensure precise estimates of key parameters. A sample size of approximately 80,000 patients is required for the development of a clinical prediction rule for this outcome, assuming an event rate of 24.6 per 100,000 person years,^41^ a median follow up of 7 years,^42^ a conservative estimate of Nagelkerke’s R^2^ statistic of 0.15 and a maximum number of 40 parameters per model.  Feasibility counts showed that this sample size is adequate for the development of the prediction rules. Since Intracranial bleeding is the rarest of the primary outcomes to be studied, the sample size will be sufficient for all other outcomes of interest. For validation, Vergouwe *et al.,*^43^ consider at least 100 events per sample population to be “substantial” and we will comfortably exceed this in our validation cohorts for each outcome of interest.  For analyses using causal inference methods (propensity score matching and instrumental variable analysis), assuming clinically significant increased rate of each adverse event with treatment of 10%, and an event rate of at least 0.5% per year in the non-exposed group, approximately 88,380 patients (44,190 in each group) and 4,634 events will be required to accurately define the relationship between preventative treatment and adverse events, with 90% power and an alpha of 0.05. |

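### The haemorrhage rate behind the 80,000 sample size does not fit the 1,200 events in the feasibility count, and the 90% power stated for Aim 3 does not extend to haemorrhage

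*Protocol*

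**What the plan says.** Under *Feasibility counts*, after restriction to linked English practices and the eligibility criteria, "the expected population is approximately 3.3 million". Among these patients the protocol expects 216,000 falls, "230,000 myopathy/muscle pain events and 1,200 intracranial haemorrhage events". It gives no person-years and no breakdown by exposure cohort.

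Under *Sample size considerations*, the haemorrhage model is said to need about 80,000 patients, "assuming an event rate of 24.6 per 100,000 person years", with "a median follow up of 7 years", "a conservative estimate of Nagelkerke’s R^2^ statistic of 0.15" and "a maximum number of 40 parameters per model". The rate and the follow-up both come from cited literature. The target shrinkage and the maximum attainable R² are not given. The protocol then concludes: "Feasibility counts showed that this sample size is adequate for the development of the prediction rules". Because haemorrhage is the rarest primary outcome, it extends that conclusion to every other outcome.

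For the causal analyses (Aim 3), the same section asks for 88,380 patients and 4,634 events. This is to detect a 10% increase with 90% power at alpha 0.05, given at least 0.5% per year in the unexposed.

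The primary outcomes are "Falls; Myopathy/muscle pain; Intracerebral haemorrhage". The outcome table lists intracerebral haemorrhage under antiplatelets and also under statins. Antiplatelet patients enter three months after a first cardiovascular event; the size of that cohort is not stated.

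**The concern.** Two adjacent paragraphs describe the same outcome with figures that do not fit together, and one of them is used to certify the other. If the lower rate is right, 80,000 patients would supply about 29 haemorrhages for up to 40 parameters. The 80,000 is the only development sample size stated, and every other model's adequacy is argued from it. Amendment 2 also withdraws the internal validation, so this calculation carries more of the protection against overfitting.

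The labels add to the uncertainty. The outcome tables, and the title of the review cited for the rate, say intracerebral. The feasibility and sample size text says intracranial. The count and the modelled outcome are therefore not shown to be the same event.

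For Aim 3, a reader would take the 90% power to cover all three primary outcomes. Haemorrhage is far rarer than the event rate on which that power depends.

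**Working it through.** **Inputs from the protocol:** rate 24.6 per 100,000 person-years; 7 years; Nagelkerke R² 0.15; 40 parameters; 3.3 million patients; 1,200 events; 4,634 events for Aim 3. **Assumptions:** the 7-year median serves as mean follow-up; target shrinkage S = 0.9.

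**1. Reproducing 80,000.** The shrinkage criterion is n = 40 / [(S − 1) × ln(1 − R²cs/S)], where R²cs = 0.15 × maxR² and maxR² = 1 − exp(2 lnL₀/n). With e = rate × 7 = 0.001722, the null log-likelihood per patient is e·ln(e) − e (risk form; the binary form is almost identical) or e·ln(rate) − e (exponential form).

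| Form | maxR² | n | Events |
|---|---|---|---|
| Risk or binary, unrounded | 0.0250 | about 95,600 | 165 |
| Exponential, unrounded | 0.0316 | 75,856 | 131 |
| Any form, maxR² rounded to 0.03 | 0.03 | 79,800 | 137 |

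The rounded version reproduces the stated 80,000.

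**2. The two rates.**
- Events expected at the stated rate: 0.000246 × 7 × 3,300,000 = 5,683, against 1,200.
- Rate implied by the count: 1,200 / (3,300,000 × 7) = 5.2 per 100,000 person-years.
- Ratio: 24.6 / 5.19 = 4.7. With mean follow-up of 5 years it is 3.4, and with 3 years 2.0.

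The figures agree if mean follow-up is (1,200 / 3,300,000) / 0.000246 = 1.5 years, or if the 1,200 come from 1,200 / (0.000246 × 7) = about 697,000 patients.

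**3. Required size at the feasibility rate.**

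| Form | maxR² | n | Events |
|---|---|---|---|
| Risk or binary, unrounded | 0.0065 | about 371,000 | 135 |
| Exponential, unrounded | 0.0079 | 304,722 | 111 |
| maxR² rounded to two decimals | 0.01 | 239,800 | 87 |

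With 80,000 patients, the stated rate gives 80,000 × 0.001722 = 138 events. The feasibility count gives 80,000 × 1,200 / 3,300,000 = 29.

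**4. Aim 1 adequacy.** Across both rates the criterion needs about 87 to 165 events. The protocol expects 1,200, which is about 7 to 14 times as many.

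**5. Aim 3.** The Freedman formula with equal groups gives (1.960 + 1.282)² × [(1.10 + 1)/(1.10 − 1)]² = 10.507 × 441 = 4,634, which is the protocol's figure. With 1,200 events, √(1,200/441) − 1.960 = 1.650 − 1.960 = −0.310, a power of about 38%. The assumed 0.5% per year is 500 per 100,000: 500 / 24.6 = 20 times the stated haemorrhage rate, and 500 / 5.19 = 96 times the feasibility rate. For illustration, 90% power with 1,200 events needs (HR + 1)/(HR − 1) = √(1,200/10.507) = 10.69, so HR is about 1.21.

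**The case against.** The strongest reply is that nothing fails for Aim 1. The number of events required barely moves with the rate, and 1,200 exceeds it many times over. The 3.3 million patients also exceed 371,000. This stands, provided the events belong to the cohort in which the model is fitted. A reader might infer that the haemorrhage model is too small; the documents do not support that.

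A second reply is that a literature rate and a database count need not match. The 7 years is a median from another study, and no person-years are given for the 3.3 million. The limitations section also warns that harms may be under-recorded and that linkage raises recorded rates. These are fair explanations, but the protocol offers none of them for this count. A gap remains at 3 and at 5 years.

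Four further readings are tempting and go too far:
- *That 305,000 is the required size.* It is one form of the formula with an assumed shrinkage, and that form returns 75,856, not 80,000, at the protocol's own inputs.
- *That the two rates lead to opposite Aim 3 conclusions, because 5,683 exceeds 4,634.* That would need every event in 3.3 million patients to fall in equal treated and untreated groups. Both rates are far below the assumed 0.5% per year in any case.
- *That the intracranial label makes the true gap larger.* The label mismatch is real, but the documents do not show which events were counted.
- *That haemorrhage is modelled only after a cardiovascular event.* It is also a statin outcome; the point about cohort entry concerns the primary-outcome model.

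**Conclusion.** The point holds as an unreconciled conflict between a rate and a count, with a missing denominator. The gap is 4.7-fold if mean follow-up is 7 years. At the feasibility rate, 80,000 is too small under every form tried, and the requirement is about 240,000 to 371,000 (40 parameters, Nagelkerke R² 0.15, shrinkage 0.9 assumed).

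Aim 1 adequacy survives if the 1,200 events lie in the modelled cohort. For the primary outcome that is the antiplatelet cohort, and the protocol does not show it.

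For Aim 3, the stated 90% power is not delivered for haemorrhage. The protocol's own count gives at most about 38% at a hazard ratio of 1.10, assuming equal groups and no events beyond the CPRD GOLD count. Restriction to new users (Amendment 1) and, in the matched analysis, 1:1 matching can only reduce the usable events. This conclusion does not depend on which haemorrhage rate is right.

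**What to change.** - Use one outcome label throughout: intracerebral, as in the outcome tables.
- State patients, person-years and expected haemorrhages in the antiplatelet cohort, and say which denominator the 1,200 belong to.
- Reconcile the 24.6 per 100,000 with that count, or explain the difference.
- Rerun the sample size calculation with that cohort's rate, showing the target shrinkage and maxR², and restate the required size.
- Judge adequacy against that cohort's patients and events.
- For Aim 3, state the achievable power, or the detectable hazard ratio, for haemorrhage separately instead of leaving 90% to be inferred.

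The cost is a recalculation and the rewording of one section. No new patients, data or analyses are needed. The downside is a less favourable stated size and power for haemorrhage.

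### The 90% power claimed for the causal analyses does not hold for haemorrhage, the antiplatelet primary outcome, and the figure contains no allowance for the instrumental variable analysis

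*Protocol*

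**What the plan says.** Everything at issue is in Part 2 of the protocol, under Feasibility counts and Sample size considerations.

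- **Causal calculation.** One figure is given for propensity score matching and instrumental variable (IV) analysis together. The effect is set by "assuming clinically significant increased rate of each adverse event with treatment of 10" per cent; the control rate and the resulting requirement are "an event rate of at least 0.5% per year in the non-exposed group, approximately 88,380 patients (44,190 in each group) and 4,634 events", "with 90% power and an alpha of 0.05". No follow-up time and no instrument strength are stated.
- **Prediction-model calculation, just above it.** This is based on intracranial haemorrhage, described as the least common primary outcome, "assuming an event rate of 24.6 per 100,000 person years" and "a median follow up of 7 years".
- **Feasibility counts.** In about 3.3 million eligible CPRD GOLD patients the protocol expects 216,000 falls, "230,000 myopathy/muscle pain events and 1,200 intracranial haemorrhage events".

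Intracerebral haemorrhage is listed as a primary outcome and belongs to the antiplatelet exposure (Outcomes to be measured; Exposures, Outcomes and Covariates). The protocol uses both intracranial and intracerebral; I treat them as one outcome. None of the four amendments revises the sample size section.

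**The concern.** The prediction-model calculation is built on the rarest primary outcome. The causal calculation drops that principle: it assumes a rate that haemorrhage does not approach, yet is worded for each adverse event. A reader would conclude that all three drug groups have 90% power for a 10% harm. For antiplatelets the protocol's own counts say otherwise.

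This matters because the study is labelled hypothesis testing and its harm estimates are to feed a decision tool. A non-significant haemorrhage result reported against a stated 90% power invites more reassurance than the data could give. The IV analysis matters too, because its agreement with the propensity score result is one of the protocol's checks for unmeasured confounding.

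**Working it through.** **Inputs from the protocol.** Hazard ratio (HR) 1.10; alpha 0.05, taken as two-sided because that reproduces the figure; power 90%; control rate 0.5% per year; 1:1 groups; haemorrhage rate 24.6 per 100,000 person-years; 1,200 haemorrhages, 216,000 falls and 230,000 muscle events in 3.3 million patients.

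**1. Reproduce the stated figure.** Freedman's two-group log-rank formula:

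events = [(HR + 1)/(HR − 1)]² × (1.95996 + 1.28155)² = (2.1/0.1)² × 3.2415² = 4,633.8, i.e. 4,634. This matches.

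With 10 full years at 0.5%, control risk is 5% and treated risk is 1 − 0.95^1.1 = 5.486%, mean 5.243%. Then N = 4,633.8/0.05243 = 88,380. This matches too. So 88,380 rests on 10 years of complete follow-up, which the protocol does not state for this calculation.

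**2. Compare haemorrhage with the assumptions.**

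- Rate: 0.5%/0.0246% = 20.3, so the assumed floor is about 20 times the protocol's haemorrhage rate.
- Events: 1,200/4,634 = 26% of the requirement.

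**3. Power and detectable effect with 1,200 events, split 1:1.**

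- Power at HR 1.10 = Φ(√1,200 × 0.1/2.1 − 1.96) = Φ(1.650 − 1.960) = 0.38.
- Detectable HR at 90% power: (HR + 1)/(HR − 1) = √1,200/3.2415 = 10.69, so HR = 11.69/9.69 = 1.21.

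This is favourable to the plan, since it places every GOLD haemorrhage in the comparison. Matching discards patients, and antiplatelet entry requires a first CVD event. If all events were kept but exposure were unbalanced, power would be about 33% at 70/30 and 26% at 80/20 (illustrative splits).

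**4. Are the two haemorrhage inputs consistent?** 3,300,000 × 7 years × 24.6/100,000 = about 5,680 events, not 1,200. Conversely, 1,200/(3,300,000 × 7) = 5.2 per 100,000 person-years, not 24.6.

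**5. Falls and muscle pain.** Expected proportions are 216,000/3,300,000 = 6.5% and 230,000/3,300,000 = 7.0%. In 88,380 patients these give about 5,785 and 6,160 events, and power of about 95% and 96% by the formula in step 3. The claim holds for these outcomes in a direct two-group comparison.

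**6. IV analysis.** The formula in step 1 has no instrument term. Required events rise by about 1/ρ², where ρ is the instrument–treatment correlation. The protocol gives no ρ, so these values are illustrative only:

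| Assumed ρ | Multiplier | Events needed | Power at 4,634 events |
|---|---|---|---|
| 0.1 | 100 | 463,400 | 6% |
| 0.2 | 25 | 115,850 | 10% |
| 0.4 | 6.25 | 28,963 | 25% |

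**The case against.** **Haemorrhage.** The 1,200 is a GOLD count. The protocol extracts data from GOLD and Aurum and names no database for Aim 3, so the 38% is a ceiling for GOLD only. That stands as a qualification, but the protocol gives no Aurum count, and doubling to 2,400 events would raise power only to about 65%. It can also be said that patients with a prior CVD event may bleed more often than 24.6 per 100,000. The protocol gives no rate for that cohort, so a reader should not convert the general rate into a number of post-CVD patients required. A higher rate would not rescue the claim within GOLD, because 1,200 is the count for the whole eligible population. If instead the rate is right and the count wrong, about 5,680 events would arise, but 4,634 is 82% of those, so most of the 3.3 million would have to be in the antiplatelet comparison.

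**Follow-up.** A reader might infer that the 7-year median contradicts 88,380: at exactly 0.5% per year over 7 years, that number gives about 3,245 events and 77% power, and about 126,000 patients would be needed. The document does not support this as a contradiction. The 7 years is given only for the prediction model, 10 years matches the primary prediction horizon, and 0.5% is a floor that falls and muscle pain exceed (step 5). What remains is that the 10-year assumption is unstated.

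**IV.** A reader might infer that the IV analysis is hopelessly imprecise throughout. That does not follow either. Instrument strength is unknown, and 88,380 is a minimum, not the planned size. If all 216,000 falls were used, power would be about 99% at a correlation of 0.2 and 60% at 0.1. What stands is that a figure with no instrument term cannot be claimed for the IV analysis.

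**Null result.** Nothing in the protocol says that a null haemorrhage result will be read as no harm. The proposed wording is a safeguard.

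**Conclusion.** The calculation is not an arithmetic error: both stated numbers reproduce. The fault is that a correct figure is applied to an outcome that fails its assumption. For one of three primary outcomes the stated 90% power is wrong as written. On the protocol's own 1,200 events it is about 38% for HR 1.10, and 90% power is reached only at HR about 1.21; matching would make both less favourable. This rests on a two-sided test, 1:1 groups, the GOLD count, and reading intracranial and intracerebral haemorrhage as the same outcome.

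The haemorrhage rate and count also disagree by a factor of nearly five (5,680 against 1,200). The IV claim is unsupported in direction, but its size cannot be fixed from the document. For falls and muscle pain the propensity-matching claim stands.

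**What to change.** Revise Sample size considerations as follows.

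1. Limit the 90% power claim to outcomes that meet the 0.5% per year floor, naming falls and muscle pain.
2. For haemorrhage, state that the study is not powered for HR 1.10, give the detectable HR (about 1.21 or more at 1,200 GOLD events), and say that a null result will not be interpreted as absence of harm.
3. Reconcile the haemorrhage rate with the expected count, and update the detectable HR if the count changes or Aurum is used for Aim 3.
4. State the 10-year follow-up and 5% control risk on which 88,380 rests.
5. Remove the claim that the figure covers the IV analysis, or restate it with an explicit instrument-strength assumption and label the result illustrative.

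The cost is rewording. No more patients or data are needed. The downside is that the stated figures become less favourable.
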